## Funder

This study is being funded by the Thalidomide Trust.

*This protocol describes the 'EVALUATION OF THE PERIPHERAL NERVOUS SYSTEM IN PATIENTS WITH THALIDOMIDE-INDUCED LIMB MALFORMATIONS' study and provides information about procedures for entering participants. The protocol should not be used as a guide for the treatment of other participants; every care was taken in its drafting, but corrections or amendments may be necessary. These will be circulated to investigators in the study, but centres entering participants for the first time are advised to contact the trials centre to confirm they have the most recent version.*

## **EXECUTIVE SUMMARY**

### **BACKGROUND**

- Thalidomide was introduced as a sedative agent in the UK in the 1950's. It was withdrawn from use in 1961 as a result of serious side-effects and congenital limb malformations, documented in babies born to mothers taking the drug during pregnancy.
- There is some evidence suggesting that the pathobiological abnormalities associated with Thalidomide use may be due to damage of the neural crest in the embryo and a peripheral neuropathy induced in adults. The mechanisms, however, have still to be precisely established.
- Characteristically, Thalidomiders have gross defects of the upper limbs (less so lower limbs) and a range of musculo-skeletal abnormalities. Thalidomide embryopathy results in well documented clinical profiles, involving various face and special sense anomalies, cranial nerve lesions, cardiovascular malformations and physiological abnormalities.
- Assessment of beneficiaries and feedback from Heath Link [Trust Helpline] has documented a major and escalating health problem, accentuated by the ageing process and resulting in increasing disability and morbidity, especially involving the musculoskeletal and peripheral nervous system.

### **PURPOSE OF STUDY**

- The Trustees are very much aware of the substantial morbidity encountered by the beneficiaries, accentuated by the ageing process, and the very poor management of many of these problems in most of the beneficiaries in the UK. This is due to the rarity of the condition and inadequate support by the NHS due to lack of appropriate clinical experience and expertise and a very poor understanding of the likely causes of the major clinical problems experienced by the beneficiaries – pain (severe, stabbing, burning) pins and needles, numbness, joint problems and muscular disorders.

### **AIM OF STUDY**

- The aim of this study is to characterise, using established clinical and investigational tools, any peripheral neuropathy (sensory, motor, sympathetic) in middle-aged beneficiaries.

## LAY SUMMARY AND COMMENTARY

The Trustees of the Thalidomide Trust are very much aware of the substantial and significant morbidity encountered by the thalidomiders, accentuated in an escalating manner by the ageing process, and the limited management of and support provided by the NHS in the UK. The Trustees are concerned about these medical (and psychological) problems and have empowered the Health and Welfare Group (H&WG) in the Trust to address these issues and how they may be resolved or improved.

The H&WG, with representation from the National Advisory Committee (NAC), after comprehensive discussions and with the approval of the Trustees, has established a modest Health Link infrastructure to provide information and support to those beneficiaries seeking help and guidance about their condition, and to direct and facilitate their access to those aspects of the NHS (primary and tertiary) which would provide the necessary and appropriate level of support and treatment.

An important element of the Health Link set-up is the creation of an anonymous Register, to record and collate the clinical features (and psychological concerns) experienced by the beneficiaries, defining more precisely the spectrum of disorders and their frequencies, in the beneficiaries registered with the Trust. The information gathered, to-date, has confirmed the need for such a service and highlighted the complexity of the medical problems. It has also documented the poor level of support and benefit provided for Thalidomiders by the NHS in the UK.

There are a variety of reasons for this very poor management of most beneficiaries. Firstly, the abnormalities of anatomy and tissue function found in Thalidomiders are limited to a small, albeit important, group of individuals. This rare clinical condition, and low national priority, has inevitably led to a dearth of clinical experience and expertise in the NHS. Secondly, the symptom complex in most beneficiaries is multi-factorial, very poorly understood and the contribution of different causes, including any thalidomide-induced peripheral nerve damage, is unclear and often confusing.

This failure of understanding the basic elements contributing to the clinical problems and lack of the necessary clinical expertise has contributed to the poor quality of advice provided and treatment offered to Thalidomiders.

The H&WG also established a sub-group/committee to explore the feasibility of carrying out a pilot project to study a small cohort of Thalidomiders (and healthy controls), identified with significant and relevant symptoms (pain, numbness, pins and needles, involving joint and muscles).

The purpose of this study is to define more precisely the contribution of peripheral nerve damage to the complex symptoms experienced by the beneficiaries. Hopefully, this may lead to a more specific, targeted and more beneficial therapeutic approach to be used in patient management.

We have identified a group of specialists with the necessary expertise ([name], [name] and [name]), based at the West London Neurosciences Centre, Charing Cross Hospital, London. We are fortunate in collaborating with this Centre of excellence. The study is perceived as being mutually advantageous as [name] are interested in studying this area.

A formal Report, with an accompanying Lay Document, will be produced and presented to the Trustees for information, evaluation and any further action by the Trust.

Prior to any presentations or publications in the public domain the intended material will be accessible to the Trustees and their Medical Advisors for their comment and due acknowledgement will be given to the Thalidomide Trust.

## **1. BACKGROUND**

### **1.1 Introduction**

1.1.1 Thalidomide (alpha-phthalimido-glutarimide) is believed to have been developed in the 1940s and may have been tested in Nazi-occupied France and possibly in concentration camps in Poland (1). It was subsequently evaluated by Gruenenthal as an anticonvulsant agent, shortly after World War II. It was found to be unsuitable for this purpose but shown to have sedative properties. It was demonstrated to be an effective drug and overdoses were not lethal (2). It replaced barbiturates from 1957 (Germany) onwards, until it was withdrawn towards the end of 1961 (later in Japan). It was removed from use in the UK (marketed as Distavel) as a result of the serious side-effects (irreversible peripheral neuropathy) and devastating congenital malformations, documented in babies born to mothers taking the drug during pregnancy (2, 3).

1.1.2 Recently, it has been introduced as a treatment for certain groups of adult patients with myeloma (3). In such patients, peripheral neuropathy has been shown to occur due to damage of the mature and fully developed peripheral nervous system.

1.1.3 When assessing patients, it will be difficult to differentiate any specific thalidomide-induced neuropathy from a range of extrinsic factors and abnormalities arising as a consequence of the severely disturbed growth and anatomical anomalies eg (phocomelia) in the limbs. Abnormal stresses on normal or improperly developed joints due to repeated and long-term patterns of activity results in premature and exacerbated osteoarthritis (eg cervical spondylosis), chronic muscular strain and inflammatory changes in fibrous connective tissues and tendons.

1.1.4 Also, unrelated (non thalidomide-induced) factors such as the thoracic inlet syndrome, nerve entrapment on crossing the humerus and carpal tunnel compression, may contribute to the symptoms and defective function documented in Thalidomiders. Hence, all these various contributing factors may make it difficult to establish the presence of any intrinsic thalidomide-induced neuropathy.

## **1.2 Possible Modes of Action**

1.2.1 McCredie in her recent book (2), suggests the drug damages the neural crest of the developing embryo, thereby, causing abnormal sclerotome developments. This postulate, supported by experimental evidence in animals, offers an explanation for many of the observed outcomes in humans. However, this theory, does not explain the apparent resistance to neural damage in the segments above and below C5, 6 and 7 in the upper part of the body. Moreover, there is no such resistance in naturally occurring limb reduction defects, as a consequence of hereditary or idiopathic causes.

1.2.2 Central nervous system and associated developmental defects of the special senses (ear, eye), as well as certain cranial nerves, may also occur. The Vth , Xth , XIth and XIIth cranial nerves appear to escape damage ([name] – personal communication, 2009). Various syndromes (Crocodile Tear, Duane and Marcus Gunn) have, in the past, been linked to thalidomide-induced damage.

1.2.3 Differences in the axiality of limb reduction defects found in sporadic or genetic causes of phocomelia, are highlighted when compared with thalidomide-induced changes. In the latter, only the pre-axial (C5, C6, C7) pattern occurs in the upper limbs. In the former, both pre-axial and post-axial patterns (C8, T1) are found. In both axial patterns, complete absence of the limbs can occur. In the post-axial pattern, high 'amputation-like' limb deficiencies may occur, above the elbow and without digit buds.

1.2.4 Autonomic nervous system dysfunction is not well studied nor well documented. [name], in over 50 years of clinical practice and working as a Medical Advisor to the Trust, has recorded only a few examples of bladder dysfunction (personal communication, 2009). As far as we are aware, there have been no clinical and laboratory studies of bowel, bladder, sexual and vascular autonomic function carried out and the findings published in peer-reviewed journals.

1.2.5 A recently published study from Aberdeen suggested that thalidomide may also have a detrimental effect on blood vessel development by inhibiting angiogenesis.

## **1.3 Thalidomide Embryopathy**

Clinical profiles that have been documented in Thalidomiders include:

1.3.1 **Limb Abnormalities:** upper limb abnormalities are the commonest but both upper and lower extremities can be affected, very rarely lower limb defects alone. Preaxial reduction defects, from hypoplasia, of the thumb (or, alternatively, thumb triphalangism) to total limb absence can occur. Limb reduction defects occur bilaterally in 80 – 85% of cases, though with a variable degree of asymmetry.

- a) *Hypoplasia of first and second digits* – typical abnormality with hypoplasia of supporting carpal bones and variable long bone defects (deficiency of radius), with or without deficiency of glenoid process of scapula and associated subluxation of the shoulder.
- b) *Ulna shortening* - is less pronounced than that of the radius and may be the only long bone, fused to a humeral remnant and supporting the fourth and fifth digits, close to the shoulder.
- c) *Phocomelia* ('seal limb') - is the term given to a very short, paddle shaped arm with two or three digits.
- d) *Thumb triphalangism* – where the thumb is changed to an index finger-like digit arising next to the index, with wrist and forearm preserved. Rarely the thumb may be duplicated.
- e) *Foot abnormalities* – hypoplasia of the great and second toes occur with reduction defects of the tibia, but there may be instead (quite frequently) big and second toe duplication leading to a polydactylic foot. The foot itself is usually preserved virtually intact though frequently in a club foot position.

1.3.2 **Musculo-skeletal System:** Abnormalities of muscle, connective tissues, spine and pelvis are present to a variable degree.

- a) *Muscles* – may be hypoplastic, fused, absent or have abnormal insertions; function in adult thalidomiders appears normal, but strength is impaired if the muscle is under developed or works with a mechanical disadvantage from abnormal anatomy. Hypoplastic preaxial and surviving postaxial fingers (ie 4th, 5th), even if of normal length, may nevertheless show flexion deformities and limited movement, probably from tendon shortening.
- b) *Spine* – abnormalities of the inter-vertebral discs and epiphyseal plates occur resulting in anterior fusion of adjacent vertebral bodies with the associated kyphosis or scoliosis. Prominent ossification of the anterior spinous ligament with loss of flexibility is

seen. In the cervical spine, especially, spondylosis of the intervertebral joints is common spondylolysis / spondylolisthesis may occur at L5. Spina bifida occulta and, less frequently, spinal canal stenosis also occur in thalidomiders.

c) *Bony pelvis* – shows varying degrees of aplasia with sacrum being malformed or partly absent, absent pubic ramus, deficient or absent hip socket.

## 1.4 Health Link

1.4.1 The ageing process may affect the Thalidomide Trust beneficiaries differentially, contributing to increased perceived disability and morbidity.

Through the Health Link Helpline set up by the Trust, the following have been identified:

**Musculoskeletal Problems:** These include shoulder, neck, hip, and back

**Pain:** Chronic, with an unidentified source

**Pins and Needles:** As shown by the questionnaire statistics below. This is a very common symptom amongst the beneficiaries.

**Abnormal Sweating:** This is beginning to show up as quite a common symptom. However, it was commonly reported in childhood, and ‘explained’ (with little evidence) on the basis of reduction of surface area available for cooling.

**Accidents:** Are becoming a common problem, particularly because of a lack of understanding by Health Care workers that if already disabled a fairly minor loss of function can destabilise a situation and render the individual much more severely disabled. Unfortunately, we have had a couple of instances of “accidents” during medical or surgical treatment.

1.4.3 In 2008, a postal survey with 175 responders self-reported neuropathic symptoms (pain, numbness, tingling) to be a problem in 75% of cases.

## **2. PURPOSE OF THE STUDY**

The purpose of the study, therefore, is to define more precisely the contribution of peripheral nerve damage, irrespective of the cause, experienced by the Thalidomiders.

## **3. AIM OF STUDY**

To characterise, using established clinical and investigational tools, any peripheral neuropathy (sensory, motor and sympathetic) in a cohort of middle-aged Thalidomiders.

## **4. STUDY PROTOCOL**

### **4.1 REC Approval**

Clinical study and patient enrolment will only commence when approval has been given by the Research Ethics Committee.

### **4.2 Thalidomiders and Healthy Volunteers Studied**

Twenty thalidomiders will be enrolled into the study. Cohort of patients will be screened and selected for possible participation from the Health Link Register. The Thalidomide Trust will contact the thalidomiders' GP/PCT and will ask for a referral for them to be seen at Charing Cross. Once the referral is received by the PIs of the study, the thalidomiders will be invited to attend their study visit at Charing Cross Hospital.

Ten healthy volunteers (carers or friends of thalidomiders accompanying them) will also be invited to take part in the study.

### **4.3 Inclusion Criteria**

4.3.1 Patients identified from the Register will be invited to participate in the clinical study.

Healthy volunteers, aged between 18 to 65 inclusive and with no neurological or musculo-skeletal disorders, will also be invited to participate.

4.3.2 Patients and healthy volunteers will have read and understood the Patient and Healthy Volunteer Information Sheets, respectively, and signed the appropriate Informed Consent forms.

4.3.3 All thalidomiders enrolled will have upper limb anomalies and clinical features suggestive of peripheral and / or central nervous system abnormalities.

4.3.4 All invitees will be able to undergo the neurological examination, nerve conduction studies, sympathetic skin responses and thermal threshold testing, albeit limitations may be imposed by anatomical abnormalities.

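### Controls may be aged 18 to 65 while the patients are a narrow middle-aged birth cohort, which leaves the neurophysiological comparison open to confounding by age

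*Protocol*

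**What the plan says.** Section 4.3.1 of the protocol sets the control criteria: "Healthy volunteers, aged between 18 to 65 inclusive and with no neurological or musculo-skeletal disorders". Section 4.2 names the source: "Ten healthy volunteers (carers or friends of thalidomiders accompanying them"). Sections 4.2 to 4.4 contain no rule that matches or bands the volunteers by age.

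For patients there is no numeric age limit. Section 3 aims to characterise neuropathy "in a cohort of middle-aged Thalidomiders". Their ages can be inferred from section 1.1, which says of the drug: "It replaced barbiturates from 1957 (Germany) onwards, until it was withdrawn towards the end of 1961 (later in Japan"). The Executive Summary dates UK withdrawal to 1961. Section 1.2.4 cites a personal communication of 2009, so the protocol was written in or after that year.

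The volunteers are controls: the Lay Summary and section 5.2.2 both use that word, and no other reference group is named. Under section 4.5.2 they attend one session, for the neurophysiological assessments. Section 5.1.1 says only that the data will be analysed statistically.

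**The concern.** The two groups are drawn from very different age ranges. Exposure before birth fixes the patients' ages within a few years, while a control may be anyone from 18 to 65 who comes along on the day. If nerve conduction, sympathetic skin responses and thermal thresholds shift with age, a difference in mean age between the groups becomes a difference in the measurements that has nothing to do with thalidomide.

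The direction depends on who the companions are. Younger companions would make ordinary ageing in the patients look like neuropathy. Older companions could hide a real abnormality. Sections 1.1.3 and 1.1.4 already warn that intrinsic neuropathy will be hard to separate from other causes. An uncontrolled age difference adds one more explanation, and this one can be avoided at enrolment.

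**Working it through.** The protocol states no test, significance level, effect size or SD, so there is no figure of its own to reproduce. The following shows how large the problem could be.

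**Patient age.** Births of about 1958 to 1962 are inferred from the dates of use. A study year of 2009 to 2012 is assumed.
- Youngest: 2009 − 1962 = 47.
- Oldest: 2012 − 1958 = 54.
- About 50 is used as the reference age.

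**How far a control may lie from a patient aged 50.**
- Younger by up to 50 − 18 = 32 years, or older by up to 65 − 50 = 15 years.
- Only 10 of the 47 eligible years (21%) lie within 5 years of 50.

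**Gap if controls were spread evenly over 18 to 65 (assumption).**
- Mean age (18 + 65)/2 = 41.5, so the gap is 50 − 41.5 = 8.5 years.
- SD of age 47/√12 = 13.57 years.

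**Spurious difference in SD units.** Let r be the correlation between age and outcome over ages 18 to 65. The range 0.3 to 0.5 is assumed, since the protocol gives no age relation for these measures. With the age effect linear, and the SD taken among people of equal age:

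d = r × gap / 13.57 / √(1 − r²)

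- Gap 8.5, r = 0.3: 0.3 × 8.5 / 13.57 / 0.954 = 0.20.
- Gap 8.5, r = 0.5: 0.5 × 8.5 / 13.57 / 0.866 = 0.36.
- Gap 5: 0.12 and 0.21 by the same formula.

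**False-positive rate.** Take a two-sided 5% t test of 20 v 10 (assumed), 28 degrees of freedom, critical value 2.048, and non-centrality d / √(1/20 + 1/10) = d / 0.387.

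| Gap in mean age | d (r = 0.3 to 0.5) | Rejection rate with no true effect |
|---|---|---|
| 0 years | 0 | 5% |
| 5 years | 0.12 to 0.21 | 6.0% to 8.3% |
| 8.5 years | 0.20 to 0.36 | 7.8% to 14.7% |

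These rates are per measure. They apply equally to older controls if the sign is reversed, but the bias then works against finding neuropathy.

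**Where an age slope would come from.** Under even spread, the controls contribute 9 × 13.57² = 1,657 to the within-group sum of squares for age. Patients spread evenly over 47 to 54 contribute 19 × 7²/12 = 78. The controls' share is 1,657 / 1,735 = 96%, so the slope used for any adjustment would come almost wholly from 10 people.

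**The case against.** **The limits permit an imbalance but do not create one.** This stands. Carers and friends may be close to the patients in age, and the protocol does not say. A reader might infer that the comparison is confounded; the documents support only that it is open to confounding. Nor do they say that every patient is about 50. That is an inference from dates.

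**The controls are not the yardstick for everything.** This also stands. Sensory, motor and reflex findings (sections 4.6.1 to 4.6.3) are graded on scales that contain their own normal grade, and needle EMG (section 4.6.7) looks for neuropathic or myopathic changes directly. No section says that neuropathy will be diagnosed from a difference in group means. The point is confined to the neurophysiological comparison with the volunteers.

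**Much larger error rates can be produced.** A 15-year gap with r = 0.5 gives 36%. That needs both the strongest assumed correlation and a sample skewed towards the young, which nothing in the protocol establishes.

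**Analysis could deal with it.** The SAP is not shown, so the absence of an adjustment is no finding, and it would be too strong to say that adjustment cannot help. If controls really were spread evenly, adjustment would widen the standard error by a factor of only √((0.15 + 8.5²/1,735)/0.15) = 1.13, provided the age effect is linear. It fails where it is most needed. If controls clustered 15 years below the patients with an SD of 5 years (assumed), the within-group sum of squares would be 9 × 25 + 78 = 303 and the factor √((0.15 + 15²/303)/0.15) = 2.4. In both cases the slope and the linearity rest on 10 people, so adjustment is a weak substitute for a sensible age range at entry.

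**Conclusion.** The concern holds as a weakness of design. The control age range in section 4.3.1 is far wider than the patients' inferred range of 47 to 54, and nothing in the protocol keeps the groups comparable in age. Under the stated assumptions the likely size is moderate: about 0.20 to 0.36 SD and a false-positive rate of about 8% to 15% per measure if companions are spread evenly over the permitted ages, about 6% to 8% at a 5-year gap, and no inflation if the mean ages agree. This rests on the age dependence of the measures (general knowledge, not stated in the protocol), the correlations of 0.3 to 0.5, a linear effect, and a simple two-group test that the protocol does not specify.

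A reader might see this as a defect that invalidates the study. The documents do not support that: this is a 30-person pilot with a descriptive aim, and the actual imbalance is unknown. It is a should-fix. The time to act is before the controls are tested, because the £12,000 grant in section 5.2.2 is to cover all 30 subjects and leaves no stated provision for a second set.

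**What to change.** In section 4.3.1, replace the 18 to 65 limit for volunteers with the enrolled patients' actual age range plus or minus about 5 years. On the inferred ages that is 47 − 5 to 54 + 5, or roughly 42 to 59, and it should be reset once real ages are known. Alternatively, frequency-match the controls to the patients on age. In either case report age by group.

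A window of 42 to 59 is centred on 50.5, the midpoint of the patients' inferred range, so controls spread evenly within it would leave almost no gap in mean age.

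The cost is recruitment. If companions were spread evenly over 18 to 65 (assumption), 17/47 = 36% would qualify. One companion for each of 20 patients would then yield about 7, short of 10, and about 10/0.36 = 28 companions would have to be considered. Finding 10 controls may therefore take longer or mean approaching more than one companion per patient. If companions are mostly contemporaries of the patients, the cost is small, and so is the bias being prevented. No extra subjects or procedures are needed.
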